## Abstract

**Background:**

Gas embolism induced by CO_2_ pneumoperitoneum is commonly identified as a risk factor for morbidity, especially cardiopulmonary morbidity, after laparoscopic liver resection (LLR) in adults. Increasing pneumoperitoneum pressure (PP) contributes to gas accumulation following laparoscopy. However, few studies have examined the effects of PP in the context of LLR. In LLR, the PP-central venous pressure (CVP) gradient is increased due to hepatic vein rupture, hepatic sinusoid exposure, and low CVP management, which together increase the risk of CO_2_ embolization. The aim of this study is to primarily determine the role of low PP (10 mmHg) on the incidence of severe gas embolism.

**Methods:**

Adult participants (*n* = 140) undergoing elective LLR will be allocated to either a standard (15 mmHg) or low (10 mmHg) PP group. Anesthesia management, postoperative care, and other processes will be performed similarly in both groups. The occurrence of severe gas embolism, which is defined as gas embolism ≥ grade 3 according to the Schmandra microbubble method, will be detected by transesophageal echocardiography (TEE) and recorded as the primary outcome. The subjects will be followed up until discharge and followed up by telephone 1 and 3 months after surgery. Postoperative outcomes, such as the Post-Operative Quality of Recovery Scale, pain severity, and adverse events, will be assessed. Serum cardiac markers and inflammatory factors will also be assessed during the study period. The correlation between intraoperative inferior vena cava-collapsibility index (IVC-CI) under TEE and central venous pressure (CVP) will also be explored.

**Discussion:**

This study is the first prospective randomized clinical trial to determine the effect of low versus standard PP on gas embolism using TEE during elective LLR. These findings will provide scientific and clinical evidence of the role of PP.

**Trial status:**

Protocol version: version 1 of 21-08-2020

**Trial registration:**

ChiCTR2000036396 (http://www.chictr.org.cn). Registered on 22 August 2020.

**Supplementary Information:**

The online version contains supplementary material available at 10.1186/s13063-021-05678-8.

## Background

Laparoscopy is a common surgical treatment for various hepatic diseases, largely due to the enhanced recovery after surgery [1]. CO_2_ pneumoperitoneum is necessary for laparoscopy to achieve sufficient operative space. Pneumoperitoneum-related gas embolism is a serious complication in patients who undergo laparoscopic liver resection (LLR), which increases the risk of mortality and postoperative complications [2, 3]. Multiple factors, including pneumoperitoneum pressure (PP), affect gas accumulation at both the tissue and cellular levels.

Currently, the PP range of about 15 mmHg is commonly used in LLR. Increasing the PP can change the surgical peritoneal environment and lead to peritoneal dissemination and hypoxia [4–6], which may eventually cause respiratory and circulatory injury [7]. In LLR, the PP-central venous pressure (CVP) gradient is enlarged due to hepatic vein rupture [8], hepatic sinusoid exposure, and low CVP management, all of which increase the risk of CO_2_ embolization [9]. Therefore, a low level of 6–10 mmHg PP is recommended in laparoscopic surgery, according to recent studies [10, 11]. A low PP has been shown to improve postoperative pain and may also decrease liver and kidney injuries [12]. The link between intraperitoneal pressure and embolization has been demonstrated in experimental animal models [13]. However, the effect of PP level on gas embolism during LLR has not been comprehensively delineated among patients.

Transesophageal echocardiography (TEE) is invaluable in patients with cardioembolic events because of its high sensitivity and specificity for defining the detailed structure and function of the cardiovascular system [14]. In addition, there is a strong correlation between the TEE-derived inferior vena cava (IVC) diameter and the CVP [15]. The IVC collapsibility index (IVC-CI) is inversely correlated with CVP [16], but this correlation may be invalid in LLR when a high PP is added [17].

### Objectives

The aim of the present study was to assess the effects of standard (15 mmHg) versus low PP (10 mmHg) on the occurrence and severity of gas embolism using TEE during elective LLR, to evaluate the corresponding postoperative recovery with the Post-Operative Quality of Recovery Scale (PQRS) [18], and attempt to explore the correlation between IVC-CI and CVP on postoperative outcomes.

### Trial design

GASES is a prospective, randomized, controlled, assessor-blinded, two-arm trial initiated by investigators. The contents of this protocol are based on the recommendations for interventional trials (SPIRIT) guidelines [19]. The SPIRIT checklist is included in Additional file 1. In total, 140 patients will be randomly assigned to one of two different PP (CONSORT diagram, Fig. 1).

**Fig. 1 Fig1:**
[figure not shown]
CONSORT flowchart illustrating the randomization and flow of study participants. LPP, low pneumoperitoneum pressure; SPP, standard pneumoperitoneum pressure; POD, postoperative day

The GASES trial tests the hypothesis that, in patients undergoing laparoscopic liver surgery, low PP (10 mmHg), compared to standard PP (15 mmHg), reduces the incidence of severe gas embolism, which will be recorded as the primary outcome. Severe gas embolism is defined as gas embolism ≥grade 3 in the right atrioventricular system from the four-chamber cardiac plane of the middle esophagus, as detected by TEE (GE VENUE R2) during the LLR according to the Schmandra microbubble method [20].

## Methods/design

The GASES trial will be conducted during laparoscopic hepatectomy (patients diagnosed with hepatic tumor, hemangioma, and hepatic cyst) at Zhongshan Hospital Fudan University, Shanghai, China.

### Selection of participants

Patients will be included in the GASES trial if they comply with the inclusion and exclusion criteria outlined below:

### Inclusion criteria

For inclusion, adult patients must meet all the following criteria:
Patients scheduled to perform elective LLR under general anesthesia18–75 years oldBody mass index (BMI) between 18.5 kg/m^2^ and 30 kg/m^2^From whom written informed consent is obtainable either from the patient or from a legal representative

### Exclusion criteria

Patients will be excluded for any of the following reasons:
Patient with acute heart failurePatient with acute coronary insufficiencyPatient with severe renal failure (defined as creatinine clearance < 30 mL/min or requiring renal replacement therapy)Patient with preoperative shock (defined as the need for vasoactive drugs before surgery)History of neuromuscular disease and abdominal cancer with adhesionContradiction to use TEE because of severe esophageal varicesParticipation in other drug trials in the 30 days prior to enrollmentParturient or breast-feeding womenInability to express oneself correctly, poor compliance, and inability to complete the test according to the study planPatient’s or relative’s refusal to participate

### Randomization and blinding

Randomization will be conducted over a dedicated, password-protected, SSL-encrypted website (edc.fudan.edu.cn) to allow immediate and concealed allocation. Each patient will be given a patient number and randomization number. The allocation sequence, with an allocation ratio of 1:1 for each group, will be generated using a minimization algorithm stratified according to risk of intraoperative exposure of the hepatic vein, liver cirrhosis status, and history of abdominal surgery. Participant allocation will be performed by a specific local investigator; the investigator will log into the randomization system using a personal ID code and will enter any relevant information. This will ensure that the patient receives only surgery under the randomized PP. The process of sequence generation and storage will be managed by an independent database manager who is not involved in patient care.

Surgeons and assessors of intraoperative gas embolism grades and PQRS [21] will be blinded to the treatment allocation. At least two assessors will be involved in the study. One assessor will determine the intraoperative gas embolism grades, and the second assessor will perform postoperative visits and assessments of the primary and secondary endpoints. All patients will be followed up by researchers who are blinded to the intraoperative grouping, and each patient will be evaluated by the same researcher during the perioperative period.

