**Fig. 2 Fig2:**
[figure not shown]
Schedule of enrolment, interventions, and assessments. Pre-op, pre-operative; PACU, post-anesthesia care unit; POD, postoperative day; CVP, central venous pressure; IVC-CI, inferior vena cava-collapsibility index; PQRS, Post-Operative Quality of Recovery Scale

The patients will be screened according to the inclusion criteria. All patients meeting the inclusion criteria will be registered in a screening log file. The investigators will explain the course and purpose of the study and provide written information on the study. Patients willing to participate in the study will be required to provide written informed consent (Additional file 2).

Data will be registered in both the paper case report form (CRF) and the electronic case report form (eCRF) on electronic data capture (EDC) system by trial or clinical personnel under the supervision of the trial investigators. In the case of inconsistency, the paper CRF will be used as a gold standard.

The following data will be collected:

Pre-randomization and baseline characteristics: Demographic data, including age, height, weight, sex, and BMI; surgical characteristics, including preoperative diagnosis, and type, location, number, and size of the primary liver tumor; co-morbidities, including coronary heart disease Y/N and Canadian Cardiovascular Society (CCS) score if Y, chronic heart failure Y/N and New York Heart Disease Association (NYHA) score if Y, atrial flutter or fibrillation Y/N, premature systole Y/N, conduction block Y/N, pulmonary ventilation dysfunction Y/N, chronic obstructive pulmonary disease Y/N and specific therapy if Y, hypertension Y/N, diabetes mellitus Y/N, chronic alcoholism Y/N, obstructive sleep apnea-hypopnea syndrome Y/N, and active smoking Y/N; American Society of Anesthesiologists (ASA) physical status; preoperative use of statins Y/N; preoperative use of aspirin Y/N; biological indices, including CRP, hs-CRP, c-TnT, NT-proBNP, IL-1, IL-6, IL-8, and IL-10; values of blood routine examination, hepatic and renal function, and coagulation function; measurements at baseline in the operation room (without oxygenation) before anesthesia induction, including measurements of heart rate, respiratory rate, CVP, SpO_2_, non-invasive blood pressure (NIBP), invasive blood pressure (IBP), artery blood gas (ABG) analysis and cerebral oxygen saturation (PQRS-0 is measured pre-operatively as the baseline).

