At randomization (stratification): risk of intraoperative exposure of hepatic vein Y/N, liver cirrhosis status Y/N, and history of abdominal surgery Y/N.

During the surgical procedure, the TEE probe will be placed through the esophagus until extubation, and the following data will be collected:
Anesthetic data: type and doses of hypnotics, opioids, and muscle relaxants; duration of anesthesia; total volume of maintenance fluid; total number of blood products; ventilator settings (VT, respiratory rate, PEEP, FiO_2_); baseline (and then hourly) values for P_ET_CO_2_; cerebral oxygen monitoring values; blood pressure (systolic, diastolic, and mean); cardiac index, stroke volume variation, and cardiac performance index measured by the PULSION medical system (not mandatory); infusion rate of vasoactive drugs (dobutamine, ephedrine hydrochloride, noradrenaline, and other), and hourly urine output.Surgical data: type of surgery, duration of surgery, total volume of blood loss, surgical complications Y/N, and surgeon satisfaction.Intraoperative TEE monitoring data: intraoperative gas embolism grade, baseline for IVC-CI, and eccentricity index (EI) after anesthesia induction, and the grades and duration during gas embolism occurrence. EI is used to evaluate right ventricular volume and pressure overload [23]. IVC-CI and EI will also be recorded at the time of trocar insertion, the beginning of hepatic parenchymal transection, hepatic tumor removal, and following completion of the surgery. Vital signs, CVP, P_ET_CO_2_, cerebral oxygen monitoring values, ABG, and IVC-CI will also be recorded when any grade of gas embolism is detected by TEE.

After the surgical procedure, the following indices will be collected before hospital discharge:

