#### Primary outcome

The effects of the intervention on the incidence of severe gas embolism in the right ventricular system detected by TEE will be reported as numbers and percentages estimated with risk ratios and 95% confidence intervals (CI), as calculated by Wald’s likelihood ratio approximation test and with *χ*^2^ tests for hypothesis testing.

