#### Subgroup analyses

Treatment effects on the incidence of gas embolism will be analyzed according to the following subgroups: (1) plan of exposing the hepatic vein versus without planning, (2) history versus without history of abdominal surgery, and (3) with versus without liver cirrhosis. The effects on subgroups will be evaluated according to the interaction effects between each subgroup and the study arms using generalized regression models and presented in a forest plot.

Per-protocol analyses: The per-protocol population will consist of patients who truly operate with the pre-specified protocol. Thus, patients will be excluded from this population if they receive PP < 15 mmHg in the standard PP group or PP > 10 mmHg in the low PP group, in any measurement during the surgery.

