Complications related to gas embolism should be considered carefully, as gas embolism resulting from pneumoperitoneum establishment has been shown to be associated with a 28% mortality rate after laparoscopic cholecystectomy [32]. CO_2_ gas embolism in laparoscopic surgery may also cause postoperative cardiac arrest [2], cerebral infarction [3], and even death [33]. We reported a case of CO_2_ embolism during laparoscopic nephrectomy without evidence of right-to-left shunt, in which the patient suffered from slurred speech and developed epileptiform seizures 9 h after the surgery [34]. Once gas embolism occurs during LLR, it may affect cardiopulmonary function and even cause neurologic deficits, resulting in delayed postoperative recovery. In this study, TEE will be used for gas embolism monitoring because it is capable of detecting 0.02 mL/kg of gas. Cerebral oxygen will also be observed to prevent cerebral embolism caused by micro emboli. TEE has no effect on cerebral oxygen because the baseline values are mainly related to cardiac function [35].

The occurrence of CO_2_ embolism likely depends on several variables. Surgical duration and size of parenchymal transection are likely to be directly proportional to the risk of gas embolism [36]. Intraperitoneal pressure may also play a role. Indeed, a higher PP led to higher degrees of embolization after laparoscopic IVC injuries in anesthetized pigs [13]. Hence, low-PP surgery is attractive, especially in reducing the incidence of embolism and its related complications. In addition, clinically, the most important benefit of low-PP is lower postoperative pain scores, which accelerate postoperative recovery [12]. No previous studies have compared the incidence of gas thrombosis in low versus standard PP during elective LLR. Therefore, we hypothesized that a low PP (10 mmHg) with controlled-low-CVP will lead to less severe gas embolism and promote postoperative recovery as compared to standard PP (15 mmHg) in elective LLR. To better evaluate the prognosis, PQRS will be used to assess recovery after LLR according to six dimensions of health, including physiologic, nociceptive, emotive, activities of daily living, cognitive, and overall patient perspective [18].

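### Transection size is named as a likely driver of gas embolism, but no preoperative measure of resection extent enters the minimisation or the stated primary analysis; prespecifying one as a covariate is a cheap improvement.

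*Protocol article*

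**What the plan says.** - **Allocation** (Protocol article, Randomization and blinding): 1:1 minimisation, "stratified according to risk of intraoperative exposure of the hepatic vein, liver cirrhosis status, and history of abdominal surgery". Study visits and data collection lists the items entered at randomisation: "risk of intraoperative exposure of hepatic vein Y/N, liver cirrhosis status Y/N, and history of abdominal surgery Y/N".
- **Risk drivers**: the Discussion states "Surgical duration and size of parenchymal transection are likely to be directly proportional to the risk of gas embolism". The Background also points to the pressure gradient between abdomen and central veins, which in this operation "gradient is enlarged due to hepatic vein rupture", and to sinusoid exposure and low central venous pressure.
- **Primary analysis** (Primary outcome): counts, percentages and a risk ratio with 95% confidence interval, with chi-square "tests for hypothesis testing". No covariate is named.
- **Subgroups** (Subgroup analyses): the three minimisation factors again, the first being "plan of exposing the hepatic vein versus without planning".
- **Case mix** (Methods/design): "patients diagnosed with hepatic tumor, hemangioma, and hepatic cyst". The inclusion criteria set no limit on the extent of resection.
- **Baseline data** (Study visits and data collection): before randomisation the trial records the preoperative diagnosis and "type, location, number, and size of the primary liver tumor".

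**The concern.** The protocol's own reasoning ties transection size to the primary outcome, yet nothing known before surgery about the size of the planned resection is used in allocation or in the stated test. Two of the three minimisation factors, cirrhosis and previous abdominal surgery, are not linked to embolism anywhere in the article. The third, hepatic vein exposure, is linked and may partly track extent. A yes/no exposure item does not measure transection size, however: a small lesion beside a vein and a large peripheral resection would be coded in opposite ways.

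At about 70 patients per arm, the arms could differ by chance in the share of large resections. An unadjusted estimate would carry that difference. Ignoring a prognostic baseline variable can also cost some precision.

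**Working it through.** **Plan's own figure.** Inputs from Sample size: 45% versus 69%, two-sided 5%, 80% power, 10% drop-out. With the unpooled formula, n per arm = (1.960 + 0.842)² × (0.45×0.55 + 0.69×0.31) / 0.24² = 7.849 × 0.4614 / 0.0576 = 62.9, so 63 per arm and 126 in total. Then 126 / 0.9 = 140. The plan's figures reproduce, and this point does not change them.

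**Assumptions.** The documents give neither the share of large resections nor their effect on risk. I take a share q of 30–50% and an odds ratio of 2–5 for severe embolism, with an average risk of (45 + 69)/2 = 57%. Extent is treated as independent of the minimisation factors. If it tracks hepatic vein exposure, the imbalance will be smaller.

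**Chance imbalance.** SD of the between-arm difference = √(2q(1−q)/n).

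| n per arm | q | SD (points) | P(difference > 10 points) |
|---|---|---|---|
| 70 | 0.3 | 7.7 | 20% |
| 70 | 0.4 | 8.3 | 23% |
| 70 | 0.5 | 8.5 | 24% |
| 63 | 0.3 | 8.2 | 22% |
| 63 | 0.5 | 8.9 | 26% |

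**Effect on the estimate.** Shift in the risk difference = imbalance × risk difference between large and small resections. Worked case, q = 0.4 and odds ratio 3: the risks that average to 57% are 46.7% and 72.4%, a gap of 25.7 points. A 10-point imbalance then shifts the result by 0.10 × 25.7 = 2.6 points. A 1.96-SD imbalance at 70 per arm shifts it by 1.96 × 0.0828 × 25.7 = 4.2 points. Over the whole assumed range the shift is 1.6–3.7 points per 10 points of imbalance. At 1.96 SD it is 2.5–6.2 points with 70 per arm and 2.6–6.5 with 63. The planned difference is 24 points.

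**Validity and power.** Simulation with 63 per arm, q = 0.4, no balancing on extent, 6,000 trials per setting, comparing the chi-square test with logistic regression adjusted for a perfectly measured binary extent:

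| Odds ratio for extent | Chi-square type I error | Chi-square power | Adjusted power |
|---|---|---|---|
| 2 | 5.1% | 80.5% | 79.7% |
| 3 | 5.2% | 80.3% | 80.6% |
| 5 | 5.3% | 80.4% | 83.4% |

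A repeat with 20,000 trials gave chi-square against adjusted power of 80.2/79.2, 80.2/80.7 and 79.7/82.3%. Chi-square type I error was 5.6–5.9%, including when extent had no effect at all, so the small excess belongs to the test at this sample size and not to extent. A Mantel-Haenszel test stratified on extent (3,000 runs) gave 83.4% against 80.7% at odds ratio 4, and 84.5% against 80.8% at odds ratio 6. With a proxy that classifies extent correctly in only 75% of patients, adjusted power was 78.7–79.1% at odds ratios 2–5, which is no gain. These models contain extent alone, without the three minimisation factors.

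**The case against.** A trial need not balance or adjust for every suspected risk factor. Three were chosen, and one of them, hepatic vein exposure, belongs to the protocol's stated mechanism. The unadjusted chi-square test is valid under randomisation, and its confidence interval already allows for chance imbalance. Covariate adjustment is often left to a statistical analysis plan, which is not shown here. All of this stands, and it limits the point to an improvement.

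Four stronger readings are tempting and are not supported:

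- *Transection size is the strongest driver, left to chance.* The Discussion says only that it is likely, names it jointly with surgical duration, and ranks nothing. The Background names other drivers, and no effect sizes are given.
- *The minimisation is wrong.* No passage requires extent to be a factor, and leaving it out contradicts nothing.
- *The primary result would be biased.* There is no systematic bias. What remains is a possible imbalance in the one sample obtained, and some lost precision.
- *The needed item is already collected.* Planned major versus minor resection is not among the listed baseline items, and type of surgery is listed with data gathered during the procedure. Tumour size is recorded at baseline but is only a proxy, and it may be undefined for patients with cysts.

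The list of diagnoses suggests that resections will vary in size, but the article gives no extents. The objection does not remove the mismatch between the stated rationale and the stated analysis, nor the low cost of closing it.

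**Conclusion.** The point holds as a low-cost improvement to the stated primary analysis, and not as a fault in the allocation. The protocol links transection size to the primary outcome, and neither the minimisation nor the stated primary analysis uses a preoperative measure of it. Under the assumed ranges, an imbalance above 10 points has roughly a one-in-five to one-in-four chance and would move the estimate by a few points out of 24. A shift of 5–6 points needs both a strong effect of extent and an imbalance of the size seen in about one trial in twenty. The power at stake is about 0–4 points. It is nil or slightly negative if extent is weakly prognostic or poorly measured. The size of the benefit therefore rests on figures that the documents do not give.

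**What to change.** Leave the minimisation as it is; enrolment began in October 2020 (Trial status). Before unblinding, prespecify one pre-randomisation measure of resection extent:

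- preferably planned major versus minor resection, taken from the preoperative surgical plan by someone unaware of allocation; or
- otherwise baseline tumour size, with a stated rule for cysts and multiple lesions.

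Enter it with the three minimisation factors in a covariate-adjusted risk-ratio analysis of the primary outcome, for example a standardised risk ratio from a logistic model. State whether this analysis or the chi-square test decides the primary conclusion. Do not adjust for actual transection size or operating time: both arise after randomisation and may be affected by the assigned pressure.

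Cost: a few lines of analysis text and one more model term. Tumour size needs no new data, whereas planned extent needs abstraction from preoperative records. The downside is that precision may not improve.
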